### Participant timeline {13}

We aim to investigate 56 interventions in cirrhotic patients with coagulation abnormalities at the study sites. We will recruit patients from both outpatient clinics and inpatient wards who are scheduled for an upcoming invasive procedure, and who would usually be considered for blood components as bleeding prophylaxis prior.

The schedule of enrolment, intervention and assessments is displayed in Fig. 2. All patients meeting eligibility criteria will have a blood sample taken within 24 h of their upcoming planned procedure (72 h for stable outpatients). If platelets and/or INR are within the range that the patient would normally be given FFP or platelet transfusion prior to the procedure as per standard of care (institution-based), ROTEM analysis will be performed, and the patient will proceed to the randomisation phase.

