## Interventions

### Explanation for the choice of comparators {6b}

The RECIPE trial is designed to compare ROTEM-guided blood component prophylaxis with standard of care blood component prophylaxis in patients with cirrhosis having invasive procedures.

At the time of our protocol development, there had been no previously published ROTEM decision-making algorithm for patients with cirrhosis having invasive procedures. The ROTEM-based algorithm we have developed is based on those that have been published for use in other settings (liver transplant and cardiothoracic surgery [26]) and then modified by an expert panel of haematologists (co-investigators HN and CH).

For our standard of care arm, the INR and platelet cut-offs used to guide blood component prophylaxis have not specifically been defined and instead will be at the discretion of the individual study sites and proceduralists. This decision was made on the basis of previous work published by our team which found significant heterogeneity in routine prophylactic transfusion practices across Australian institutions for different procedures and different trigger INR and platelet cut-offs [18].

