### Intervention description {11a}

All participants will have baseline pathology including standard coagulation testing and a ROTEM analysis.

ROTEM analysis will be performed by one of the investigators using the ROTEM-sigma device located at the study site, within 4 h of the participant’s blood draw. The ROTEM-sigma performs all analyses on citrated whole blood and will be run according to the manufacturer’s instructions. Each blood sample will be tested using four ROTEM assays with different reagents provided by the manufacturer: each of these assays evaluates overall clot formation and strength. The EXTEM evaluates clot formation mimicking the conventional extrinsic pathway, INTEM evaluates clot formation mimicking the conventional intrinsic pathway, FIBTEM evaluates the contribution of fibrinogen to clot formation, and APTEM which evaluates any antifibrinolytic effect. All other laboratory tests will be run by the Hospital pathology laboratories at the study sites.

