### Concealment mechanism {16b}

Site investigators will contact the coordinating site who will run the computer-generated randomisation and allocate the participant to the randomised allocation. Based on the allocation, the site study investigators will determine the prophylactic blood product (if any) required and liaise with the treating time to see if this is ordered before the procedure. The proceduralist and participant will not be aware of the participant’s allocation.

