### Implementation {16c}

The site investigators at the individual sites will enrol participants. Once enrolment is complete, the coordinating site will run the computer-generated randomisation and allocate the participant to an intervention arm.

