## Assignment of interventions: blinding

### Who will be blinded {17a}

Participants will be blinded to the results of their ROTEM analysis and will not be told whether they are assigned to the ROTEM-based arm or standard of care. However, it is possible that those participants who end up not requiring prophylactic blood product transfusion may deduce that they have been randomised to ROTEM-based decision-making. The proceduralist will also be blinded to the allocation. The study investigator and treating team are not able to be blinded, as it is necessary for these staff to order and administer the blood products. The person performing the randomisation will be blinded to the result of the ROTEM analysis. Given the hard outcomes of the study, we do not think the lack of blinding of the treating clinicians will greatly bias the results.

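### ROTEM is run before randomisation, and no one who enrols or decides transfusion is said to be kept from the result, although the primary efficacy outcome is that transfusion decision

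*Protocol article*

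**What the plan says.** All references are to the protocol article.

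- **Order of steps.** Under Participant timeline {13}, blood is taken and INR and platelets are compared with the institution's own transfusion range. If they fall within it, "ROTEM analysis will be performed, and the patient will proceed to the randomisation phase".
- **Who runs the test.** Intervention description {11a}: "ROTEM analysis will be performed by one of the investigators using the ROTEM-sigma device located at the study site", within 4 h of the blood draw.
- **Who enrols.** Implementation {16c}: "The site investigators at the individual sites will enrol participants". The coordinating site then runs the randomisation.
- **Who decides the product.** Concealment mechanism {16b}: once the allocation is known, "the site study investigators will determine the prophylactic blood product (if any) required".
- **Standard-of-care rule.** Explanation for the choice of comparators {6b}: the cut-offs "have not specifically been defined and instead will be at the discretion of the individual study sites and proceduralists". The standard of care description in the Interventions section adds that they may differ by site and procedure.
- **Blinding.** Who will be blinded {17a}: "Participants will be blinded to the results of their ROTEM analysis". The person who randomises is also blinded to the result, but the study investigator and treating team are not blinded. On the proceduralist: "The proceduralist will also be blinded to the allocation". The section concludes that unblinded clinicians should cause little bias because the outcomes are hard ones.
- **Primary efficacy outcome.** Outcomes {12}: the proportion of procedures preceded by any FFP, platelets or cryoprecipitate.

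**The concern.** Two routes to bias are left open.

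1. **The control-arm decision.** After allocation, an unblinded site investigator who may already know the ROTEM result settles whether a standard-of-care patient receives product. That decision is the endpoint. Withholding product because ROTEM looked normal lowers the control rate and pulls the comparison towards no difference. Transfusing more readily than local practice would raises the control rate and exaggerates the effect.
2. **Entry to the trial.** If the result is known before allocation is requested, patients with abnormal ROTEM can be held back. Those enrolled would then need less product under the algorithm than eligible patients in general.

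The hard-outcome argument in {17a} is reasonable for survival. It does not fit an outcome that consists of a clinician's choice. The authors chose to shield the randomiser from ROTEM, yet the text gives no such shield for those who enrol and decide.

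There is also an ambiguity. Section {6b} gives the proceduralist a say in the cut-offs, while {16b} and {17a} keep the proceduralist unaware of the arm. A proceduralist who exercised that discretion for an individual patient after allocation would learn the arm.

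**Working it through.** **1. Chain of roles, from the text**

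| Step | Who | Kept from ROTEM result? |
|---|---|---|
| INR/platelets checked against local range {13} | site | not applicable; precedes ROTEM |
| ROTEM run {11a}, {13} | investigator at the site | no statement |
| Enrolment and request for allocation {16b}, {16c} | site investigators | no statement |
| Randomisation {16b}, {17a} | coordinating site | yes |
| Product decided, both arms {16b} | site investigators, unblinded | no statement |

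No step described records what standard of care would have given before ROTEM and allocation are known.

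**2. The protocol's sample size**

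Inputs from Sample size {14}, Statistical methods {20a} and Trial design {8}: 30% reduction, 90% power, 5% two-sided alpha, 10% loss, 1:1 allocation. The control rate is not stated. Assume 100% v 70% and use unpooled variance:

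n per arm = (1.960 + 1.282)² × [1.0×0 + 0.7×0.3] / 0.30² = 10.51 × 0.21 / 0.09 = 24.5, so 25.

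25 / 0.90 = 27.8, so 28 per arm and 56 in total, as stated. With the same formula, 95% v 65% needs 33 per arm before loss and 90% v 60% needs 39. The figure of 56 is therefore consistent with nearly every control patient being transfused.

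**3. Sensitivity to the control rate**

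Exact binomial power at 28 per arm, two-sided 0.05, ROTEM-arm rate assumed 70%:

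| Control rate | Fisher | Chi-squared (uncorrected) |
|---|---|---|
| 100% | 89% | 98% |
| 95% | 58% | 75% |
| 90% | 33% | 47% |

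In single-trial terms, with 20/28 transfused in the ROTEM arm, control 28/28 gives Fisher p=0.004 and control 25/28 (89%) gives p=0.18. Three control-arm decisions separate the two results.

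**4. Sensitivity to selective entry**

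Let q be the share of eligible patients with normal ROTEM and s the fraction of ROTEM-abnormal patients put forward. The ROTEM-arm rate among those enrolled is (1−q)s / [(1−q)s + q].

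With q = 0.30 (assumed):
- s = 1: 0.70 / 1.00 = 70%.
- s = 0.5: 0.35 / (0.35 + 0.30) = 54%.

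With control at 100%, the estimated difference moves from 30 to 46 points in this deliberately strong scenario. Both arms have the same changed case mix, so this is a different population and not an imbalance between arms.

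**The case against.** **The local trigger comes first.** Section {13} requires INR or platelets to be in the local transfusion range before ROTEM is run, and control patients are then to be treated by hospital practice. This stands, and it leaves limited room to push the control rate up. It does not close the gap: Eligibility criteria {10} ask only that the patient be considered for prophylaxis, and {16b} leaves open that no product is required.

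**Access is inferred.** No sentence says that the enrolling investigator reads ROTEM before requesting allocation. The schedule figure and the full protocol are not at hand, and progression to randomisation in {13} does not depend on the ROTEM result. This stands. Access follows from who runs the test and from who is, and is not, listed as blinded to it. A reader might infer that sites are selecting patients or steering transfusion. The documents do not support that; they show only that it is not prevented.

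**Allocation is central.** A reader might also infer that selection on ROTEM confounds the comparison. It does not: the randomiser is blinded to the result, so selection would affect both arms alike. It would change case mix, and with it the size and generalisability of the effect.

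**The magnitudes rest on assumptions.** The 100% and 70% rates are not in the protocol. Holding back half of ROTEM-abnormal patients would take about 56 / 0.65 = 86 eligible patients to randomise 56, which is hard to reconcile with the recruitment difficulty noted in the Discussion. That scenario shows direction and is no forecast.

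**The proceduralist.** It is tempting to call {6b} against {16b} and {17a} a contradiction. It is an ambiguity: a proceduralist could set thresholds in advance and remain unaware of allocation, and {8} promises only an attempt at blinding.

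**Conclusion.** The concern holds as an avoidable weakness in the design, and the protocol should be changed. The text fixes ROTEM before randomisation, in the hands of a site investigator, and does not list those who enrol and decide transfusion as blinded to it. It leaves standard-of-care cut-offs to local discretion and makes the resulting decision the primary efficacy outcome. The hard-outcome argument does not apply to that outcome.

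The consequence could be material, because the result is sensitive to the control rate. Under an assumed 70% ROTEM-arm rate and 28 per arm, moving control from 100% to 90% cuts power from 89% to 33% (Fisher) or from 98% to 47% (chi-squared). These figures show how much a few decisions would matter. They do not estimate bias that has occurred. Confidence is medium, because site access to the result before allocation is inferred.

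**What to change.** 1. **Record the intended product.** Before ROTEM is read and before allocation is requested, enter in REDCap the product that the site's own standard of care, including any proceduralist input, would give this patient. Report departures from it in the control arm. The record should not bind clinicians; it makes departures visible.
2. **Change the order.** Request allocation once INR and platelets are known; with procedural risk, these are all that the stratification in {16a} needs. Run or release ROTEM only afterwards, within the 4 h limit in {11a}. In the standard-of-care arm, do not release it to those deciding transfusion.
3. **Log eligible patients not randomised**, so that selection after screening can be seen.
4. **Reconcile the text.** State in {6b}, {16b} and {17a} whether the proceduralist only contributes to site cut-offs in advance or also decides for individual patients, and what blinding follows. Withdraw the hard-outcome statement for the primary efficacy outcome.

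The cost is one extra eCRF field, a screening log, and slightly tighter timing between blood draw, allocation and ROTEM. Where the person running ROTEM also decides transfusion, the site must arrange for the control-arm readout to stay closed to that person. The sample size is unchanged. With recruitment still open at publication, the changes could apply to patients yet to be enrolled.

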**Fig. 2 Fig2:**
[figure not shown]
RECIPE schedule of enrolment, interventions, and assessments. *Within 24 h of procedure for inpatients and 72 h of procedure for outpatients

Enrolled patients will be randomised in a 1:1 fashion to either procedure-prophylaxis guided by standard of care or ROTEM-based protocol as follows:Patients in the standard of care arm will receive blood product as per standard of care at the hospital where their procedure is taking place.Patients in the ROTEM arm will receive blood product prophylaxis according to ROTEM cut-offs (see Fig. 1 above).

Data will be collected prior to the procedure, immediately post-procedure, 7 days post-procedure and 28 days post the procedure. Data will be collected from the patient directly via medical history taking and examination, and also from the hospital’s electronic medical records.

### Sample size {14}

Previous studies using other global coagulation assays in patients with cirrhosis undergoing invasive procedures have reported a significant (at least 45%) reduction in the need for prophylactic pre-procedural transfusions [28, 29]. Assuming a modest 30% reduction in pre-procedural prophylactic use of blood products, and with a power of 90% and an alpha of 5%, and accounting for possible drop-outs and missing data of 10%, a total of 56 participants or procedures (28 in each arm) will be needed.

### Recruitment {15}

The coordinating site investigators will present the study at unit meetings at the study sites to encourage recruitment and ensure rotating staff are aware of the study. Regular email correspondence detailing screening, enrolment and study completion numbers at the various study site will be sent to all investigators.

## Assignment of interventions: allocation

### Sequence generation {16a}

Participants will undergo computer-generated randomisation using Study Randomizer [Software Application]. (2017) Available at: https://www.studyrandomizer.com. Allocation will be stratified according to procedural risk (low vs. high bleeding risk), platelet count (greater than or less than 30 × 10^9^/L) and INR (less than or greater than 2.0).

### Concealment mechanism {16b}

Site investigators will contact the coordinating site who will run the computer-generated randomisation and allocate the participant to the randomised allocation. Based on the allocation, the site study investigators will determine the prophylactic blood product (if any) required and liaise with the treating time to see if this is ordered before the procedure. The proceduralist and participant will not be aware of the participant’s allocation.

### Implementation {16c}

The site investigators at the individual sites will enrol participants. Once enrolment is complete, the coordinating site will run the computer-generated randomisation and allocate the participant to an intervention arm.

## Assignment of interventions: blinding

### Who will be blinded {17a}

Participants will be blinded to the results of their ROTEM analysis and will not be told whether they are assigned to the ROTEM-based arm or standard of care. However, it is possible that those participants who end up not requiring prophylactic blood product transfusion may deduce that they have been randomised to ROTEM-based decision-making. The proceduralist will also be blinded to the allocation. The study investigator and treating team are not able to be blinded, as it is necessary for these staff to order and administer the blood products. The person performing the randomisation will be blinded to the result of the ROTEM analysis. Given the hard outcomes of the study, we do not think the lack of blinding of the treating clinicians will greatly bias the results.

### Procedure for unblinding if needed {17b}

The chief investigator can be contacted for unblinding if necessary for patient safety.

## Data collection and management

### Plans for assessment and collection of outcomes {18a}

Baseline data will be collected from participant interviews or the electronic medical records by study site investigators at the individual study site and inputted directly into the REDCAP database. The assessment of outcomes will be in accordance with the pre-defined definitions of the outcomes such as bleeding, SAEs etc. and conducted by the Steering Committee overseeing the trial conduct. Study site investigators are all hospital doctors who have specialist expertise in the management of patients with advanced liver disease. The investigators performing the ROTEM analysis will receive formal training on how to operate a ROTEM sigma device and basic interpretation of the ROTEM analysis. by Werfen Australia.

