## Oversight and monitoring

### Composition of the coordinating centre and trial steering committee {5d}

The RECIPE trial steering committee is composed of the principal investigators and a subset of co-investigators, primarily based at the coordinating centre. The steering committee directs all aspects of the study, including protocol design, writing of the patient information and consent form, set-up and design of data collection database, monitoring of study progress and quality, and resolution of issues that arise during follow-up. Independent monitoring of study safety and quality is also provided by a DSMB (see below).

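### Procedure-related bleeding is assessed by a committee of investigators based mainly at the centre that allocates arms, and the protocol provides no masking for that assessment.

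*Protocol article*

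**What the plan says.** Five places in the protocol article bear on this point.

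- **Plans for assessment and collection of outcomes {18a}.** Outcomes such as bleeding and serious adverse events are assessed against pre-defined definitions, and this is "conducted by the Steering Committee overseeing the trial conduct".
- **Composition of the coordinating centre and trial steering committee {5d}.** The committee is "composed of the principal investigators and a subset of co-investigators, primarily based at the coordinating centre".
- **Implementation {16c}.** After enrolment, "the coordinating site will run the computer-generated randomisation and allocate the participant to an intervention arm".
- **Who will be blinded {17a}.** Participants are not told their arm. For the other roles: "The proceduralist will also be blinded to the allocation"; "The study investigator and treating team are not able to be blinded"; "The person performing the randomisation will be blinded to the result of the ROTEM analysis". The section closes: "Given the hard outcomes of the study, we do not think the lack of blinding of the treating clinicians will greatly bias the results".
- **Outcomes {12}.** The primary safety outcome is procedure-related bleeding under an international society's definition. It includes clinically significant bleeding with a haemoglobin fall of at least 20 g/L, or bleeding that leads to transfusion, readmission or intervention. Survival is to be divided into procedure-related or not.

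**The concern.** The people who classify bleeding are trial investigators. The Background section says that the investigators anticipate no difference in bleeding between the arms. They sit mainly at the centre that issues allocations, and no provision keeps the arm from them when they classify an event. If knowing the arm influences whether a bleed is called procedure-related or clinically significant, the safety comparison is biased, and the likeliest direction is towards the anticipated result of no excess bleeding with ROTEM guidance.

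The trial is small and the Background describes overall procedural bleeding risk as low, so few events should be expected. The reported bleeding rates would then rest on a handful of individual classifications.

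**Working it through.** The plan gives no figure on this point. The check is a reading of the sections together, followed by a calculation of how far one classification can move the result.

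**1. Can the assessors know the arm?**

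- Assessor: the Steering Committee ({18a}).
- Members: principal investigators and some co-investigators, mostly at the coordinating centre ({5d}).
- Source of allocation: the coordinating site ({16b}, {16c}). Site investigators are then told the arm, because they must work out the product required ({16b}). The chief investigator handles unblinding ({17b}).
- Masked under {17a}: the participant and the proceduralist. The person who randomises is masked to the ROTEM result only, not to the arm.
- Not masked under {17a}: study investigators and the treating team. Outcome assessors are not mentioned.

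So members are drawn from a group that the protocol says cannot be masked, and most work where allocation is issued. They can know the arm. The protocol does not say that they are shown it.

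**2. Which parts of the outcome need judgement?**

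- Objective measurement: the haemoglobin fall of at least 20 g/L.
- Recorded events: transfusion, readmission, intervention.
- Judgement: whether the bleed is attributable to the procedure, whether it is clinically significant, and whether a death is procedure-related.

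The hard-outcomes sentence in {17a} is offered for treating clinicians, not assessors, and it does not fit the third group. The reason {17a} gives for unmasked staff is that they must order and give blood products. That reason does not extend to classifying an event afterwards.

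**3. How much does one classification matter?**

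Inputs: 28 per arm, including a 10% allowance for drop-outs and missing data (Sample size {14}); bleeding compared per protocol by chi-squared or Fisher's exact test, two-sided at 0.05 ({20a}). No bleeding rate is given, so the event counts below are assumed.

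- Shift per event: 1/28 = 3.6 percentage points. If the whole 10% is lost, 28 × 0.9 = 25.2, so about 25 remain per arm and the shift is 1/25 = 4.0 points.
- Going from 2 to 1 events in an arm: 2/28 = 7.1% becomes 1/28 = 3.6%, half the observed rate.

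For Fisher's exact test at 28 per arm with all k events in one arm, the two-sided p is 2 × C(28,k) / C(56,k):

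| Bleeds | Calculation | p |
|---|---|---|
| 0 vs 1 | 2 × 28 / 56 | 1.0 |
| 0 vs 2 | 2 × 378 / 1,540 | 0.49 |
| 0 vs 5 | 2 × 98,280 / 3,819,816 | 0.051 |
| 0 vs 6 | 2 × 376,740 / 32,468,436 | 0.023 |

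With one bleed in the other arm the pattern is the same: 1 vs 7 gives p = 0.051 and 1 vs 8 gives p = 0.025. The observed rate is therefore sensitive to every classification. The significance test is sensitive to a single one only near these edges.

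**The case against.** The strongest reply is that no section says the committee sees allocation when it assesses an event. The unmasked investigators of {17a} are unmasked because they order and give products, which describes site staff. Data management {19} limits data access to two people at the coordinating site, so most members may see only what they are handed. The article also condenses a fuller protocol that might describe masked packs. This stands to the extent that a reader might infer that the committee works with the arm in view, and the article does not support that. It does not dispose of the point. The article itself names the assessors, says who they are, lists who is masked and argues that the remaining lack of masking is tolerable. On that account nothing masks the assessors.

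Second, several criteria are recorded facts and definitions are fixed in advance. This is correct and narrows the point to attribution, clinical significance and cause of death.

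Third, serious adverse events, bleeding in particular, go within 24 h to an independent DSMB that watches bleeding trends ({21a}). That is a partial check. The DSMB's stated role is monitoring and recommendation, not classification of outcomes.

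Fourth, a reader might infer that pre-procedure products alone give the arm away because controls are nearly always transfused. The eligibility rules make a high control rate plausible, but no rate is stated, and ROTEM patients may also be transfused. Products are a clue to the arm, not proof of it.

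**Conclusion.** The point holds as a correctable weakness in design. The assessors of the primary safety outcome can know the arm, the protocol provides no masking for them, and part of what they decide is judgement that the hard-outcomes argument does not reach.

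Its size is 3.6 percentage points per reclassified bleed at 28 per arm, and slightly more in the per-protocol set. A reader might go further and infer that a single reclassification decides the safety comparison. It does not in general: with no bleeds in the other arm, moving from 2 to 1 leaves p at 0.49 and then 1.0. Only counts such as 0 vs 5 against 0 vs 6 straddle 0.05. What one judgement reliably changes is the observed rate.

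This rests on two assumptions: that events are few, as the low risk described in the Background suggests, and that the fuller protocol contains no masking provision that the article omits. Survival itself and units transfused are not affected.

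**What to change.** Keep the Steering Committee as assessor and add to {18a}:

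1. Suspected bleeding events, their relation to the procedure and causes of death are classified from records with the arm, the ROTEM result and pre-procedure blood products removed. Products given during or after the procedure stay in, because they are part of the outcome.
2. The removal is done by a data holder at the coordinating site who does not take part in classification.
3. Members who randomised or treated the patient do not vote on that case.
4. Classifications are locked before the arm is revealed.

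In {17a}, limit the hard-outcomes sentence to outcomes recorded without judgement, such as survival and units transfused, and state whether outcome assessors are masked.

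The cost is redaction for the few suspected events among at most 56 procedures, plus the DSMB and ethics approval that {25} requires for any modification. No new assessor is needed, provided enough members remain after recusal. The fix has a limit: masked classification cannot remove the influence of unmasked treating clinicians on whether a patient is transfused, readmitted or given an intervention. That should be acknowledged when the safety result is reported.
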